**Main study goal**

The study goal is to assess the effectiveness of a counseling and testing intervention aimed at preventing primary HIV acquisition in pregnant and lactating women.

Specific objective of the formative phase:

To explore factors affecting awareness, beliefs and attitudes about primary HIV prevention among pregnant and lactating women and their partners.

Specific aims of the randomized trial phase:

- Aim 1: to assess the effect of ERHTEC on sexual risk behavior and STI and HIV acquisition in HIV-uninfected pregnant and lactating women enrolled individually
- Aim 2: to assess the effect of ERHTEC on sexual risk behavior and the incidence of STIs and HIV in HIV-uninfected pregnant and lactating women enrolled with their partner
- Aim 3: to assess the costs and estimate the cost-effectiveness of the intervention.

Specific objective of the end of follow-up qualitative assessment:

To document qualitatively the acceptability and feasibility of the intervention

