**C. DESIGN AND METHODS**

**C.1 Study Design**

We will conduct a stratified randomized trial of 820 HIV-negative pregnant women and 410 male partners in Mulago Hospital in Kampala and St Joseph District Hospital in Kitgum, Northern Uganda: in each site 205 women enrolled individually and 205 couples will be randomized to be retested and counseled either in late pregnancy (>36 weeks) only as per the WHO/MOH recommendation, or to receive the ERHTEC intervention throughout pregnancy and breastfeeding as follows:

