**C.5.2 Postpartum intervention schedule and assessments**

After the late pregnancy visit, all women and couples in the intervention arm will be asked to return at 6 weeks and 3 months postpartum and every 3 months thereafter until the end of follow-up at 24 months postpartum or 6 weeks after the end of breastfeeding, whichever occurs first. Women and couples in the control arm will be asked to return at 3 and 6 months postpartum and every 6 months thereafter until the end of follow-up at 24 months postpartum or 6 weeks after the end of breastfeeding, whichever occurs first.

Participants randomized to the intervention arms (Arms I-2 & C-2) will receive enhanced counseling at every visit and will be retested for HIV at 3, 6, 12, 18 and 24 months postpartum (or at the end of follow-up, whichever occurs first). At these visits, both intervention and control women and men participants will undergo a physical examination and will be asked to answer individually a follow-up behavioral questionnaire about their sexual behaviors, relational and reproductive intentions, including family planning. At these same visits, all women will be bled for syphilis and HIV rapid testing and two vaginal swabs will be collected, one for G/C, and Tv testing and the other for Y chromosome detection while a blood or urine sample or urethral swab will be obtained from symptomatic men for syphilis, G/C and Tv testing [*See Schedule of Events, Appendix C*].

At the end of follow-up, all study participants irrespective of their arm assignment will undergo a physical examination, will be asked to answer individually an end-of-study questionnaire and will be bled for syphilis and HIV rapid testing and a vaginal or urethral swab will be collected for G/C and Tv testing. A vaginal swab will also be collected from women to test for the presence of Y chromosomes.

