**C.5.5 Incident infections**

All participants with an incident STI or HIV infection during follow-up will receive treatment as part of standard of care provided by the hospitals and in accordance with Uganda’s National STI Treatment Guidelines[42](#_ENREF_42). These guidelines include partner notification and treatment, thus both enrolled and unenrolled partners of participants found to be infected during follow-up will be notified and treated when possible. Participants infected with syphilis and their partners will be treated with benzathine penicillin 2.4 MU IM in a single dose. Pregnant women infected with G/C or T. vaginalis and their partners will be treated with erythromycin 500mg qid for 7 days plus cotrimoxazole 2.4g bid for 3 days and metronidazole 2g single dose (no cotrimoxazole or metronidazole will be given in the first trimester or after 36 weeks of pregnancy). Non-pregnant lactating women and their partners infected with G/C or T. vaginalis will be treated with ciprofloxacin 500mg single dose and metronidazole 2g single dose plus doxycycline100mg bid for 7 days . In case of incident HIV infection in a participant, counselors will emphasize both primary & positive prevention, and a study clinician will obtain a blood sample for CD4 testing and refer the infected person(s) to Mulago or St Joseph Hospitals HIV clinic for ART eligibility assessment. All HIV seroconverters will receive cotrimoxazole prophylaxis and lifetime ART if eligible. Infected pregnant women and breastfeeding women ineligible for ART and their babies will receive PMTCT prophylaxis or treatment as per national guidelines[32](#_ENREF_32). All newly HIV-exposed infants (babies born to and/or breastfeeding from an HIV-seroconverted mother) will receive ARV prophylaxis as per national guidelines. HIV-exposed babies >6 weeks of age will be tested by HIV DNA polymerase chain reaction (PCR) assay and if infected, will be treated with triple ART at the hospital HIV clinic. Uninfected infants will be retested 6 weeks after complete cessation of breastfeeding and treated with triple ART if infected.

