**C.7 Measures**

**C.7.1 Primary outcomes**

The primary outcomes are the frequency of unprotected sex and the incidences of HIV and STI over follow-up. The trial is powered to detect a 10% difference in the frequency of unprotected sex[[2]](#footnote-3) accounting for a 50% loss to follow-up over 2 years. The frequency of unprotected sex will be determined as the self-reported number of episodes of unprotected vaginal intercourse with inconsistent or no condom use in the last 3 months and will be validated by Y chromosome detection in vaginal swabs. Reports by each partner in the couple trial will be treated as two correlated outcomes.

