In calculating STI incidence, time-at-risk will be censored for 14 days following initiation of each STI treatment. Treatment effects on incident STIs will be assessed using logistic models, with robust standard errors to account for clustering within women and couples, and inverse weighting to account for informative dropout. HIV incidence will be modeled using pooled logistic models for internal-censored failures, again with robust standard errors and inverse weighting

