**# Only symptomatic men will be tested for STIs at these time points**

**+ 24 months or** **6 weeks after the end of breastfeeding**, **whichever occurs first**

# Appendix D: End of study qualitative intervention assessments

**Theme: Acceptability and feasibility of the ERHTEC intervention**

**a) Focus group discussion points – Outline / Staff**

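### The STI incidence model in C.8.2 appears to pool male partners, who are tested between baseline and the end of follow-up only if symptomatic, although the aims define STI incidence in women

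*Protocol*

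**What the plan says.** **Endpoint and population.** C.7.1 makes STI incidence a primary outcome: "The primary outcomes are the frequency of unprotected sex and the incidences of HIV and STI over follow-up". In the Protocol Summary, Aim 2 concerns "the incidence of STIs and HIV in HIV-uninfected pregnant and lactating women enrolled with their partner", and Aim 1 likewise concerns women. C.1 plans for "820 HIV-negative pregnant women and 410 male partners".

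**Analysis.** C.8.2 gives one rule on time at risk: "In calculating STI incidence, time-at-risk will be censored for 14 days following initiation of each STI treatment". It then says: "Treatment effects on incident STIs will be assessed using logistic models, with robust standard errors to account for clustering within women and couples". Inverse weighting for dropout is added. Nothing is said about visits at which a participant attends but is not tested.

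**Testing of men.** C.4.5 tests all men at baseline, and C.5.2 tests all participants at the end of follow-up. At late pregnancy (C.5.1) only symptomatic men are tested. At the postpartum questionnaire visits a blood or urine sample or "urethral swab will be obtained from symptomatic men for syphilis, G/C and Tv testing". The footnote to the Appendix C summary table agrees: "Only symptomatic men will be tested for STIs at these time points". All women are tested at these visits.

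**Partner treatment.** C.5.5 adds that "both enrolled and unenrolled partners of participants found to be infected during follow-up will be notified and treated when possible".

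**The concern.** If men are in the STI model, one endpoint combines two kinds of ascertainment. A woman's result at an interim visit shows whether she is infected. A man's shows whether he had symptoms and was then found infected. An asymptomatic man has no scheduled test at late pregnancy or at 3, 6, 12 and 18 months, which is five of the six follow-up assessments.

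An analysis rule written later cannot supply the missing tests. The dropout weights do not help either: they address who remains in follow-up, and a man who attends untested has remained. At stake are the absolute STI rate for a named primary outcome and, if symptomatic infections are found more readily in one arm, the comparison itself.

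**Working it through.** **1. The plan's own figure.** The protocol states no rate or power for STI. Its only power figure is 80% for a 10% reduction in unprotected-sex episodes (C.8.5). With the C.8.5 inputs (410 women and 410 couples, 7 assessments, mean 5, over-dispersion 2, correlation 0.3, control reduction 30%, 50% loss), the standard error of the log ratio is 0.0369 with linear loss. Power = Φ(|ln 0.9|/0.0369 − 1.960) = Φ(2.855 − 1.960) ≈ 81%. With exponential loss the standard error is 0.0374 and power about 80%. The figure reproduces, and the present point does not touch it.

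**2. Are men in the STI model?**
- For: each couple contains one woman, so clustering within couples adds nothing to clustering within women unless the man's results are included. C.8.2 uses the same phrase for the sex-episode model, which expressly includes male partners. C.8.3 names women as the unit where it means women only.
- Against: the aims place STI incidence in women, and the STI sentence has no explicit mention of male partners.

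Inclusion is the natural reading, but it is not stated.

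**3. Size if men are pooled and untested visits are scored negative.** Men are 410/1,230 = one third of participants. Let r be men's detected infections divided by those that testing all men at every visit would find. With equal true incidence and person-time by sex (assumed), observed/true pooled rate = (2 + r)/3.

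*Simulation.* Assumptions, none from the protocol: 30-80% of male infections asymptomatic; mean duration 4-12 months; 0-50% treated through the partner; enrolment at 24 weeks' gestation; a final visit at 24 months postpartum. Loss is 50% by 18 months, as in C.8.5. Infections still present at the final all-men test are credited. Result: r ≈ 0.32 to 0.80.
- r = 0.80: 2.80/3 = 0.93, so 7% too low.
- r = 0.32: 2.32/3 = 0.77, so 23% too low.

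*Closed form.* Let s be the symptomatic share and q the share of asymptomatic infections still present at the final test (both assumed). Then r = s + (1 − s)q.

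| s | q | r | Observed/true |
|---|---|---|---|
| 0.10 | 0 | 0.10 | 0.70 |
| 0.25 | 0 | 0.25 | 0.75 |
| 0.50 | 0 | 0.50 | 0.83 |
| 0.50 | 0.50 | 0.75 | 0.92 |

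That is 8% to 30% too low over these cases. With women only, the ratio is 1.00.

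**4. If untested visits are dropped instead.** Interim male rows then come only from men with symptoms. Their positivity is not an incidence.

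**5. The arm comparison.** With the same detection in both arms, perfect specificity and the same true ratio in both sexes, a true ratio of 0.70 stays 0.70·(2 + r)/(2 + r) = 0.70.

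Equal detection is not secured, however. Under C.5.2 and the Appendix C summary, intervention participants also attend at 6 weeks and at 9, 15 and 21 months, where samples may be taken at the clinician's discretion. Controls are seen at such times only when a routine post-natal visit falls due. In the extreme case (symptomatic men sampled at all four visits, controls at none), intervention men would show about 5-23% more detected infections at equal true incidence, under the step 3 assumptions. With women's detection equal, the pooled ratio is (2 + r·k)/(2 + r), where k is the excess factor in men. Outer bounds:
- r = 0.32, k = 1.05: 2.336/2.32 = 1.007.
- r = 0.80, k = 1.23: 2.984/2.80 = 1.066.

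A null effect would thus appear as roughly 1-7% more STI in the intervention arm.

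**The case against.** The strongest reply is that the protocol does not say what is feared. A reader might infer that the full follow-up of all 410 men counts as time at risk and that asymptomatic male infections are scored as non-events. No section says either. A logistic model needs an outcome on each row, so an untested visit might simply be missing, and such handling is commonly left to an analysis plan, which is not at hand. Infections that persist are found at the final test of all men. That test comes earlier for women who wean early, which narrows the gap. C.5.5 does not say that partners are treated without being tested. With equal testing by arm the ratio need not move, and the trial is not powered on STI.

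All of this stands against the stronger reading, and it makes the 7-23% a conditional illustration. It does not remove the point. Whichever way untested visits are handled, men's interim data depend on symptoms. The clustering phrase departs from the population named in the aims, and the additional intervention visits leave equal detection unsecured.

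**Conclusion.** The concern holds in a limited form. C.8.2 appears to bring men into an STI incidence analysis that the aims define in women, while the testing schedule cannot support an incidence in men.

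The pooled rate would be about 7-23% too low only if three things hold: men are pooled, untested visits are scored negative, and the assumed asymptomatic share, duration and partner treatment apply. It would be wrong to conclude that the reported incidence will certainly be too low, or that the arm comparison is shown to be biased. The comparison is at risk only if symptomatic infections are detected unequally by arm; the illustration gives roughly 1-7% on the pooled ratio at the extreme.

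This is worth changing, because a nearly costless definition that matches the aims removes the male component of both problems.

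A separate matter is the men's flow chart in Appendix C. It puts the symptomatic-only asterisk on the control entries and not on the intervention entries, whereas C.5.1, C.5.2 and the summary table apply the rule to both arms. Those places must be reconciled in any case.

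**What to change.** In C.8.2, define the primary STI incidence analysis in women only, as Aims 1 and 2 word it, with clustering within women. Report men separately: STI prevalence by arm at baseline and at the final visit, when all men are tested, with interim symptomatic diagnoses listed descriptively and kept out of any rate.

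If the investigators do intend to include men, C.8.2 should say so and state how visits without a test enter the outcome and the time at risk.

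The cost is wording in one section, with no additional tests and no change to the sample size. The downside is that symptomatic male infections no longer count in the comparison. Separately, reconcile the men's flow chart with C.5.1, C.5.2 and the summary table.

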**C.8.3 Secondary analyses**

In calculating incidence of new pregnancies, time-at-risk will start 60 days following delivery. , Incidence of new pregnancies and MTCT will be modeled as HIV incidence above. For MTCT and new pregnancies, and infant and maternal mortality, the unit of analysis will be newborns and women participants, respectively. **Mediating factors:** The intervention is designed to enhance individual reports of partner economic and emotional support and to enhance couples’ levels of communication, mutual support and decision-making. We expect that as individuals and couple’s levels of psychosocial indices increase, they will be more likely to participate in HIV testing, less likely to engage in HIV sexual risk behavior and less likely to acquire STIs. Specifically, we hypothesize that 1) over time, intervention participants will exhibit higher scores on individual and couple-level psychosocial indices; and 2) psychosocial indices will mediate the relationship between intervention and study outcomes (HIV testing, sexual risk behavior, STI infection). **Individual-level analyses:** We will first assess whether intervention assignment impacts individual-level psychosocial variables using longitudinal mixed models. Second, we will assess whether psychosocial indices impact follow-up retention, sexual risk behavior or STI infection. Third, we will assess whether these changes in psychosocial indices mediate the effect of the intervention on subsequent HIV testing, sexual risk behavior and STI infection using the approach of Kenny[48](#_ENREF_48). This approach includes comparing estimates of the effect of the intervention on subsequent HIV testing, sexual behavior and STI infection in models with and without potential mediators. **Dyadic analyses:** In addition to the role of individual-level psychosocial variables on the intervention effect, we will also consider couple-level, (or dyadic) data, looking at actor-partner effects which allow for estimation of the effect of both partners’ psychosocial indices on each other. For example, we will consider the role of a woman’s reported communication on her own outcomes (actor effect) as well as the influence of her male partner’s reported communication on her testing and/or sexual behavior (partner effect). These analyses can be used for both continuous and categorical psychosocial variables. We will examine actor-partner effects for all of the proposed mediating variables on each of the outcomes of interest which will allow us to analyze the role that partners may play in improving the health of each other and their infants.

**C.8.4 Cost and cost-effectiveness**

We will assess the cost of individual and couple-based testing based on the current WHO and our repeat HTC schedule. We will measure the total cost, cost-per-site and cost-per-patient for the intervention and the comparison arms. We will compare the cost of individual and couple-based repeat HTC for both the current WHO recommendation as well as the ERHTEC intervention. We will estimate the cost-effectiveness of repeat HTC by estimating the number of HIV infections averted through these interventions using previously described methods. We will estimate the probability of HIV acquisition for each woman at each time point based on self-reported and validated sexual behavior, HIV and ART status of a woman’s partner and community prevalence of HIV. We will then compare the effectiveness and cost-effectiveness of both individual and couple-based repeat HTC to the controls.

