## Study concept

To our knowledge, this study will be the first randomized trial to assess an intervention promoting the primary prevention of HIV in pregnant and lactating women individually or in couples. The intervention consists in delivering extended HIV repeat testing coupled with enhanced counseling (ERHTEC) and community support throughout the lactation period with the aim of motivating and empowering women and couples to keep their baby and family free of HIV.

The enhanced counseling intervention will draw on the natural desire of pregnant and breastfeeding women and couples to keep HIV away or at bay from their baby and family. Through this approach, counselors will promote three key mother, newborn and child health (MNCH) and HIV prevention behaviors: safe sex, optimal infant feeding and care, and planning any desired subsequent pregnancy in a way that ensures optimal health of the new baby and its mother.

Counseling and education messages and guidelines need to be tailored to individual women and couples at key stages of the pregnancy and post-natal periods. In many sSA settings, the resumption of sexual activity after delivery is a critical moment for HIV prevention interventions[33](#_ENREF_33). The ERHTEC intervention will connect individual mothers and couples to family support groups including peer mothers and fathers who will be trained as mentors and lay counselors for primary HIV prevention and to support study participants to adhere to sound infant feeding practices, child care and immunization schedules, to make informed decisions regarding family planning, and to access prompt PMTCT prophylaxis and HIV care and treatment in case of incident infection of the baby and/or the mother. Couples found to be or become serodiscordant over follow-up will be referred to receive all pre-exposure prophylaxis options recommended at the time of the study, including male medical circumcision and tenofovir-based chemoprophylaxis or vaginal gel if recommended.

The study will take place in Mulago and St Joseph Kitgum hospitals that have implemented effective couple mobilization and couple HTC strategies for PMTCT that have resulted in high rates of male partner participation in antenatal, intra- and post-partum MCH care. This level of couple participation will allow us to better understand the role male partners could play in promoting and sustaining primary HIV prevention

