**C.7.5 Cost data**

Cost data will be collected annually.We will assess costs and cost-efficiency, defined as cost per client served, across all sites and intervention types (individual/couples, WHO repeat HTC/ERHTEC).We will develop a standard cost data collection protocol and manual for gathering expenditure data related to WHO and repeat HTEC in each site. Expenditures will be classified in one of 4 headings: (i) personnel; (ii) recurring goods and services; (iii) capital and equipment; and (iv) building space. In all cases, we will identify costs of providing repeat HTEC and only these costs will be included in the analysis. Capital expenditures such as computers and furniture will be amortized over 5 years of expected useful life, assuming no salvage value. Building space and other in-kind cost will be estimated using the WHO *Cost It* website[45](#_ENREF_45), which provides unit prices by region for many resources, including infrastructure, utilities and professionals’ time. .

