**The guide will address six possible retesting scenarios for individual women or couples**:

1) individual woman remaining HIV-negative

2) individual woman with incident HIV infection

3) sero-concordant HIV-negative couple

4) sero-discordant couple with HIV-infected woman

5) sero-discordant couple with HIV-infected man; and

6) sero-concordant HIV-positive couple.

For each scenario, the guide will emphasize:

- primary prevention for the individual(s) remaining HIV-negative
- positive prevention for the HIV-positive individual(s)
- disclosure, communication, sex behavior, PMTCT prophylaxis and HIV care issues.

For primary prevention, the guide will address risk behaviors and sources of potential exposure to HIV since the last test, specific vulnerabilities and risks associated with different stages of the pregnancy, delivery and postpartum periods including cultural practices and beliefs associated with sexual activity during pregnancy and breastfeeding and resumption of sexual activity after delivery.

The guide will emphasize “positive living” for both positive and primary prevention (protected sex, adequate nutrition, psycho-social support, male circumcision, avoidance of unwanted pregnancies).

In the case of serodiscordance, the guide will emphasize ART for the HIV-infected couple member, and all methods recommended for pre-exposure prophylaxis at the time of the trial such as tenofovir-based pre-exposure prophylaxis and/or microbicide gel for the HIV-uninfected couple member if recommended.

A section specific to couples will incorporate this information with the guidelines currently in use in Uganda for couple HTC including establishing the conditions for couple counselling (consent, open discussion, receiving test results together, respecting the confidentiality of shared results, joint decision about disclosure to third party), the expectations from, and roles and responsibilities of each partner (respect, equal participation, responsiveness, openness, mutual support), and the particular issues related to sero-concordance and serodiscordance of results (keeping the HIV-negative partner uninfected, ongoing care and support of the HIV-positive partner, and assessing the risk of violence or abuse and strategies for avoiding it).

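### In the couple stratum, C.8.4 sets the cost of testing and counseling two people against HIV infections averted in the woman only

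*Protocol*

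**What the plan says.** C.8.4 announces an effect measure that is not tied to sex: "estimating the number of HIV infections averted through these interventions using previously described methods". The next step narrows it to women: "We will estimate the probability of HIV acquisition for each woman at each time point based on self-reported and validated sexual behavior". The remaining listed inputs are "HIV and ART status of a woman’s partner and community prevalence of HIV". The man therefore enters as a source of risk to the woman, not as a person who can be infected.

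On the cost side, C.8.4 says "We will assess the cost of individual and couple-based testing based on the current WHO and our repeat HTC schedule", and C.7.5 collects costs "across all sites and intervention types (individual/couples, WHO repeat HTC/ERHTEC"). The stated cost-effectiveness contrast is "We will then compare the effectiveness and cost-effectiveness of both individual and couple-based repeat HTC to the controls".

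Elsewhere in the protocol:

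- C.4.5 lets partners enroll whatever their HIV status, so uninfected men are in the trial.
- C.5.1 and C.5.2 give men in the couple intervention arm the same repeat testing and enhanced counseling as women.
- Appendix B asks counselors to stress primary prevention for whichever partner is still uninfected, and includes the scenario of an infected woman with an uninfected man.
- Cost-effectiveness is Aim 3 and is listed among the primary outcomes in the Protocol Summary and the Schema.

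**The concern.** A cost-effectiveness ratio should count cost and effect over the same people, or say why it does not. In the individual stratum it does: only women are served and only women's infections are modeled. In the couple stratum the cost of involving the man is in the numerator, but an infection averted in him is not in the denominator. The mismatch affects one stratum only and can work in one direction only, as long as the intervention does not increase men's infections.

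The stakes are more than technical. The footnote to C.7.1 explains that the trial could not be powered on HIV incidence, so modeled infections averted will carry much of the HIV message. The abstract says the findings should inform policy on retesting women and their partners. A ratio that charges for partners and gives no credit for protecting them could make partner involvement look poorer value than it is.

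**Working it through.** The protocol states no count of infections averted, no cost per infection averted and no incremental ratio, so there is no figure to reproduce. The check compares the two possible definitions.

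**Formula.** Let ΔC be the incremental cost of ERHTEC over control in the couple stratum, and A_w and A_m the infections averted in women and in men.

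- Ratio as planned: ΔC / A_w
- Ratio over all participants: ΔC / (A_w + A_m)
- Overstatement factor: F = (A_w + A_m) / A_w = 1 + A_m / A_w

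F = 1 when A_m = 0, and F = 2 when A_m = A_w. ΔC cancels.

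**Inputs for an illustration.**

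- From the protocol: 205 couples per arm; follow-up to 24 months postpartum, taken as 2 years without dropout; HIV incidence in pregnant women below 2% per year (footnote to C.7.1).
- Assumed: women's incidence i_w of 1% or 2% per year; men's incidence i_m from 0 to 2% per year; the same relative reduction of 10% to 30% in both sexes; all 205 men at risk.

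Averted infections = 205 × 2 × incidence × relative reduction.

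- Women, low: 205 × 2 × 0.01 × 0.10 = 0.41
- Women, high: 205 × 2 × 0.02 × 0.30 = 2.46
- Men: from 0 to 205 × 2 × 0.02 × 0.30 = 2.46

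The relative reduction and follow-up time cancel, leaving F = 1 + i_m / i_w:

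| Men's incidence (assumed) | F if women's is 1% | F if women's is 2% |
|---|---|---|
| 0 | 1.0 | 1.0 |
| 0.5% | 1.5 | 1.25 |
| 1% | 2.0 | 1.5 |
| 2% | 3.0 | 2.0 |

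The share of infections averted that goes uncounted is 1 − 1/F, from 0 to 67% over this grid.

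**Men already infected at entry.** They cannot contribute to A_m. If a share p of the men is HIV-negative, and their absolute risk reduction is r times the women's, F = 1 + p × r. With p assumed at 0.90 to 0.95, F is 1.90 to 1.95 for r = 1, and 1.45 to 1.48 for r = 0.5.

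**Where men's risk would come from.** Every enrolled woman is HIV-negative at entry, so a man's risk within the couple is nil until she seroconverts. Before that, his risk comes from outside partners. A_m therefore depends on how far ERHTEC changes men's behavior outside the couple. The protocol gives no figure for this, so the grid cannot be narrowed.

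**The case against.** The best defense is the stated goal. The Protocol Summary and Section B define it as preventing HIV acquisition in pregnant and lactating women, and Aims 1 and 2 are framed the same way. On that view the man is a means of protecting the woman, and cost per maternal infection averted, with partner costs included, is a coherent measure. This stands in part: it justifies reporting a women-only ratio. It does not justify having no other, because C.8.4 speaks of infections averted without restriction and the counseling guide also aims to keep HIV-negative men uninfected.

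A second defense is that the man is not absent from the model. His HIV and ART status are inputs, so the benefit to the woman of his being tested and treated is at least partly captured. That is correct; only infections averted in him are missing. Third, C.8.4 leans on previously described methods that the protocol does not set out, and an analysis plan may add detail. That too is fair, but the protocol itself names the unit as the woman.

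Two stronger readings are tempting and do not hold.

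- *That leaving out PrEP and circumcision is an error.* Serodiscordant couples "will be referred to receive all pre-exposure prophylaxis options recommended at the time of the study, including male medical circumcision", and Appendix B lists circumcision among the elements of positive living: "protected sex, adequate nutrition, psycho-social support, male circumcision, avoidance of unwanted pregnancies". Neither is a listed model input. But chemoprophylaxis and gel apply only to serodiscordant couples and only if recommended. The referral is not clearly confined to the intervention arm, and equal uptake in both arms would largely cancel. C.7.5 restricts costs to those of providing the repeat testing and counseling, so costs and effects of these services appear to be left out together. Nor can one say that uptake goes unrecorded, because Table 1, to which C.6.1 points, is not reproduced in the text available.
- *That a couples-versus-individuals efficiency ranking is distorted.* C.8.4 compares individual and couple testing directly on cost only; for cost-effectiveness it compares each strategy with controls. Women are not randomized between strata. Readers may still set the two ratios side by side, but the plan does not state that contrast.

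**Conclusion.** The point holds for men's infections in the couple stratum. If the quantity wanted is cost per HIV infection averted by the intervention, the planned ratio is biased against couple-based ERHTEC by the factor 1 + A_m / A_w. That is 1.0 if infections averted in men are negligible and about 2 if they equal those in women; the grid above reaches 3.0, but only under assumed incidences. The direction rests on one assumption, that ERHTEC does not increase men's infections. The size cannot be computed from the protocol, and no distortion at all lies within the range.

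A reader might infer that the cost-effectiveness result will be wrong. The documents do not support that. If the quantity wanted is cost per maternal infection averted, the planned calculation is consistent and needs only the right label. The individual stratum is unaffected. This is a change worth making before analysis, not a flaw in the trial's design or in its behavioral primary analysis.

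**What to change.** In C.8.4, state whose infections are counted. Estimate the probability of HIV acquisition for every HIV-negative participant, including enrolled male partners. Report the couple-stratum cost per infection averted twice: over all participants, and for women only, labeled as cost per maternal infection averted.

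Little or no new data collection appears to be needed. Men are HIV-tested at enrollment, in late pregnancy and at the end of follow-up in both arms, and Appendix C schedules tests between those visits. C.5.2 has men in both arms answer the behavioral questionnaire at the main postpartum visits. The woman's HIV status is known from her own tests, and C.7.3 plans to record new and concurrent partnerships.

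The cost is added modeling and some assumptions about men's risk from outside partners, which should be varied in a sensitivity analysis. PrEP and circumcision uptake could be a further, optional sensitivity analysis if the data exist, with the cost of those services included wherever their effect is.
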